## 10.3 Data Collection Procedures for Adverse Events

### 10.3.1 Scheduled collection

#### (IDS interviews):

Item 18 =3 (suicidal ideation)

IDS total has increased >16 points since the last assessment

OR IDS total score is > 48

#### Meditation logs:

Collected at weekly sessions.

Comments sections contain possible adverse events.

Participants contacted for clarification and follow up.

#### Direct observation during sessions (weekly).

Study staff will have direct contact with participants.

Will query participants who may be having AEs

#### 3-month follow up:

Meditation Experiences Interview (MEDEX-I)

Participants queried about potentially distressing meditation experiences by independent assessor

### 10.3.2 Unscheduled collection

Participants are encouraged to contact the PI or instructor if they have any questions or problems in regard to meditation practice, their mental status or study participation.

## 10.4 Recording/Documentation

### 10.4.1 AE Reporting and Follow-Up

Adverse events and study progress will be monitored and recorded on an ongoing basis. We will use the following suggested table for reporting subject status and adverse events:

#### Status:

A = Active

C = Completed

W = Withdrew

L = Lost to Follow Up

#### % Compliance to Intervention:

% classes attended (8=100%)

## 10.4.2 Reporting Procedures

### 10.4.2.1 SAEs

SAEs that are unanticipated, serious, and possibly related to the study intervention will be reported to the Independent Monitor(s), IRB, and NCCAM in accordance with requirements. Unexpected fatal or life-threatening AEs related to the intervention will be reported to the NCCAM Program Officer within 7 days.

Other serious and unexpected AEs related to the intervention will be reported to the NCCAM Program Official within 15 days. Anticipated or unrelated SAEs will be handled in a less urgent manner but will be reported to the Independent Monitor(s), IRB, NCCAM, and other oversight organizations in accordance with their requirements. In the annual AE summary, the Independent Monitor(s) Report will state that they have reviewed all AE reports.

### 10.4.2.2 Changes in Study Status

During the funding of this study, any action of an IRB or one of the study investigators that results in a temporary or permanent suspension of the study will be reported to the NCCAM Program Official within 1 business day of notification.

## 10.5 Stopping Rules for the Protocol

This study will be stopped prior to its completion if: (1) the intervention is associated with adverse effects that call into question the safety of the intervention; (2) difficulty in study

recruitment or retention will significantly impact the ability to evaluate the study endpoints; (3) any new information becomes available during the trial that necessitates stopping the trial; or (4) other situations occur that might warrant stopping the trial.

Specifically, the occurrence of multiple severe adverse events that were definitely or probably related to meditation, in the entire intervention group, or a subgroup -would trigger an ad hoc safety review.

Enrollment and/or study intervention(s) would be suspended until a safety review is convened. The objective of the safety is a decision as to whether the study agent/intervention (for an individual or study cohort) should continue per protocol, proceed with caution, be further investigated, be discontinued, or be modified and then proceed.

### **10.5.1 Stopping Rules for an Individual Participant**

A study participant will be discontinued from further Study Intervention(s) if:

- Any clinical adverse event, laboratory abnormality, intercurrent illness, other medical condition or situation occurs such that continued participation in the study would not be in the best interest of the participant.

Development of any exclusion criteria may be cause for discontinuation.

Participant will continue to be followed with participant's permission if Study Intervention is discontinued.

### **10.6.2 Safety Review Plan**

Study progress and safety will be reviewed quarterly (and more frequently if needed). Progress reports, including patient recruitment, retention/attrition, and AEs will be provided to the Independent Monitor(s) following each of the quarterly reviews. An Annual Report will be compiled and will include a list and summary of AEs. In addition, the Annual Report will address:

- (1) whether AE rates are consistent with pre-study assumptions;
- (2) reason for dropouts from the study;
- (3) whether all participants met entry criteria;
- (4) whether continuation of the study is justified on the basis that additional data are needed to accomplish the stated aims of the study; and
- (5) conditions whereby the study might be terminated prematurely.

The Annual Report will be sent to the Independent Monitor(s) and will be forwarded to the IRB and NCCAM. The Brown IRB will review progress of this study on an annual basis.

### **10.6.3 Subject Accrual and Compliance**

#### **10.6.3.1 Measurement and Reporting of Subject Accrual, Compliance with Inclusion/Exclusion Criteria:**

Review of the rate of subject accrual and compliance with inclusion/exclusion criteria will occur every 3 months to ensure that a sufficient number of participants are being enrolled and that they meet eligibility criteria and the targeted ethnic diversity goals outlined in the grant proposal (Targeted/Planned Enrollment Table). The tables provided will be used for data collection.

#### **10.6.4 Frequency of Data Review for this Study**

The DSMB will hold at least two meetings a year with personnel in Boston and Providence meeting in person and other members outside joining by teleconference. At these meetings, the DSMB will meet first in open session attended by the study investigators and then in closed session when reviewing emerging trial data. In addition, the board will be in contact at least once a quarter in order to carry out the functions of the DSMB such as monitoring enrollment and study retention rates, reviewing patient safety, risks of participation, and protocol adherence. The DSMB will inform the Brown IRB of its findings. The aims of the study will be re-evaluated at least once a year; appropriate modifications will be made in consultation with NCCAM, if necessary.

The frequency of data review for this study differs according to the type of data and can be summarized in the following table,

| Frequency of safety review by data type                           |                            |                                          |
|--------------------------------------------------------------------------|----------------------------|------------------------------------------|
| Data type                                                         | Frequency of review | Reviewer                          |
| Subject accrual (including compliance with protocol enrollment criteria) | quarterly                  | PI, Independent Monitor(s)               |
| Status of all enrolled subjects, as of date of reporting                 | quarterly                  | PI, Independent Monitor (s)              |
| Adherence data regarding study visits and intervention                   | quarterly                  | PI, Independent Monitor (s)              |
| AEs and rates                                                            | quarterly                  | PI, Independent Monitor (s)              |
| SAEs                                                                     | Per occurrence             | PI, Independent Monitor (s)
NIH/NCCAM |

##### **10.6.4.1 Study Report Outline for the Independent Monitors(s) (Interim or Annual Reports)**

The Study Reports for the Independent Monitor(s) will follow the format provided in the sample document (enrollment, retention, demographics, AEs, SAes etc). The report will not provide data on primary or secondary endpoints, and tables will be generated only from aggregate (not by group assignment) data for the study population.

## **11. STATISTICAL CONSIDERATIONS**

## 11.1 Study overview:

The research study is part of a Career Development Award. The purpose of the research is to provide experience and training in clinical trials methodology and provide pilot data to inform a R01 application.

The trial is a 3-armed "dismantling" design, in which the standard treatment package (MBCT) is compared with individual 2 single-component treatment of the same duration. Due to the budgetary constraints of this K23 award and the pilot nature of the project, the primary objective will be to estimate treatment parameters (in contrast to absolute significance levels) for single practice modules relative to the standard package to inform a larger clinical trial [ PAR-03-078].

## 11.2 Objectives and Hypotheses:

The analysis is divided into 3 categories:

Preliminary Analysis includes assessment of delivery and acceptability of treatments, and any group inequalities that may have resulted from treatment randomization, attrition and compliance

Primary Analysis assesses: Effect of treatments on clinical outcome (negative affect/depression) and (secondary analyses) effect of treatment on mechanism of action.

Differences in clinical outcomes between active treatments tend to be small. Thus, given our sample size, we do not predict a significant difference between single-component the standard package in terms of clinical efficacy. However, because single practice interventions are less complex and easier to implement, non-inferiority to standard treatment has significant clinical meaning.

The largest group differences are hypothesized in terms of mechanism of action. Specifically, we predict: Attention training (FA) will differentially improve attention (FA>MBCT>OM)  
Acceptance training (OM) will differentially improve emotional non-reactivity (OM>MBCT>FA).

## 11.3 Analysis Plan:

### 11.3.1 Preliminary Analyses:

The purpose of the preliminary analysis is to investigate the data for patterns that may impact subsequent analyses, such as: group differences at baseline, differential attrition, compliance or instructor qualities, competence, adherence or ratings. Because we used a group randomization, we must also assess the degree to which group-ness influences outcome (i.e. intra-group correlation).

### 11.3.2 Primary Analyses:

**To asses and compare the effects of FA and OM modules on clinical efficacy vs standard MBCT** Multilevel Modeling (MLM) will be used to compare the trajectories of clinical improvements in affective states (IDS, DASS PANAS, WBS) for each treatment.

Level 1 variables will include depression, negative affect and wellbeing scores at multiple time points.

Level 2 variables will include treatment type, meditation practice amount and demographic variables (age, sex, education). A MLM approach (Bryk & Raudenbush, 1992) was chosen for analysis because it is well suited to repeated measures designs, yields more information than ANOVAs (i.e. allows for individual growth curves), has the ability to retain missing cases, and fits my training goals of advanced statistical analysis skills for treatment research.

### **11.3.3 Secondary Analysis:**

#### **11.3.3.1 To compare the effects of FA, OM and MBCT on attention, emotion regulation and wakefulness:**

A linear mixed model approach will be used to compare the effects of each treatment on each measure.

Type of treatment and time (baseline vs. post-intervention) will be modeled as fixed effects. In addition, variables identified in preliminary analysis will be added to the model as predictor variables or covariates.

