#### **Description of outcome variables:**

Attention: Changes in total SART errors (omission/commission)

Emotional Reactivity: Corrugator response ( $\log_{10} \text{ mV}^2$  for the 45–200-Hz EMG band) during first 4s of picture presentation (i.e. before meditation instruction) will be used to assess emotional reactivity to unpleasant relative to neutral pictures. This comparison reflects the traitlike effects of meditation training in the absence of deliberate affect regulation efforts.

Emotion Regulation: The 4-8s post picture onset follows FA or OM meditation instruction and therefore represents the acute affect regulation effects of *active* meditation. Emotion regulation magnitude is defined as the decrease in corrugator EMG power during 4s of meditation vs initial 4s (unregulated) response. All subjects receive both FA and OM instructions, but only the practice that corresponds to the treatment module will be used in analysis (i.e. FA-based regulation for the FA group etc). The average of the combined FA and OM-based regulation will be used for MBCT group.

Wakefulness/Sleepiness: Computer-assisted spectral analysis based EEG measurements of sleepiness will be measured by the mean log transformed power spectral density ( $\text{mV}^2$ ) of 5-9 Hz band at F3/A2, F4/A1 sites for 4 minutes. Neurobehavioral measurement of sleepiness (minutes until sleep onset) will be based on real-time visual analysis of PSG data, including EEG, eye movements, EMG (chin) tone.

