##### **11.4.4 Basic Calculations**

While effect sizes in mood and sleep following mindfulness training are large, the differences between active treatments tend to be small (Wampold et al., 1997). A sample size of 90 (30 per intervention) will be able detect a small effect size ( $d=.33$ , power  $>.80$ ,  $\alpha=.05$ ).

**Method of calculation: G\*power 3.1.3****F tests - ANOVA:** Repeated measures, within-between interaction

**Analysis:** A priori: Compute required sample size  
 $\alpha$  err prob = 0.05  
Power (1- $\beta$  err prob) = 0.80  
Number of groups = 3  
Number of measurements = 2  
Nonsphericity correction  $\epsilon$  = 1

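### The mechanism-endpoint model names treatment and time but no treatment-by-time term; fitted literally, its treatment coefficient is half the post-treatment effect

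*Protocol*

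**What the plan says.** Section 11.3.3.1 of the Protocol gives the purpose of the secondary analysis: "A linear mixed model approach will be used to compare the effects of each treatment on each measure". The specification follows: "Type of treatment and time (baseline vs. post-intervention) will be modeled as fixed effects". The only other terms allowed for are variables that emerge from the preliminary analysis.

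Three other places bear on what is to be tested:

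- Section 11.2 states the mechanism hypotheses as differences in improvement, for example "Attention training (FA) will differentially improve attention (FA>MBCT>OM"), with the reverse order for emotional non-reactivity. It expects the largest group differences on these measures.
- The description of outcome variables under Section 11.3.3.1 words the attention outcome as "Changes in total SART errors (omission/commission"). Section 5.3.2 lists SART errors without reference to change.
- Section 11.4.4 bases the sample size on the G*Power procedure "Repeated measures, within-between interaction", with three groups, two measurements, alpha 0.05 and power 0.80.

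**The concern.** Sections 7.2 and 9.4 place baseline measurement before randomization, so the expected arm difference at baseline is zero. In a model with treatment and time but no product term, the treatment coefficient averages that zero with the post-treatment difference. It therefore estimates half of what the trial wants to know and takes in half of any chance baseline imbalance.

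This matters even though the trial is a pilot. Sections 11.1 and 11.4.1 say that its purpose is to supply treatment parameters for a larger trial. Required sample size scales with 1/d², so planning from a halved effect at the same SD would inflate the next trial by a factor of (1/0.5)² = 4.

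SART has a further problem. A change score is one value per person, so it cannot also be the response in a model with a baseline-versus-post factor.

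**Working it through.** **Inputs from the Protocol (Section 11.4.4 and its output):** three arms of 30 completers, two measurements, alpha 0.05, d = .335, so f = d/2 = 0.1675.

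**Assumptions:** pre-post correlation ρ, which the Protocol does not give; equal variance at the two visits; complete data; no class effect.

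**1. Reproduce the plan's figure.** For the within-between interaction, λ = N·f²·m/(1−ρ), with 2 and N−3 degrees of freedom. At ρ = 0.5, λ = 90 × 0.1675² × 2/0.5 = 10.10 and power is 0.805. The smallest N reaching 0.80 is 89, or 90 in three equal arms. The same formula gives detectable d of .430 at alpha .005, .366 at N = 75 and .480 at N = 45. These match the stated .43, .37 and .48, so ρ = 0.5 is the value that reproduces the plan.

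**2. Change score and interaction.** With two complete time points these are the same test. In one simulated data set the interaction F and the one-way F on change scores were both 9.822.

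**3. Additive reading.** Let δ be the post-treatment difference and σ² the variance at one visit.

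- Pre/post mean: effect δ/2, variance σ²(1+ρ)/2, signal δ²/[2σ²(1+ρ)].
- Change: effect δ, variance 2σ²(1−ρ), signal δ²/[2σ²(1−ρ)].
- Ratio of noncentralities: (1−ρ)/(1+ρ).

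At ρ = 0.5, λ = 10.10 × 0.5/1.5 = 3.37 and power is 0.346. Reaching 80% would need about N = 261. In 20,000 simulated trials power was 0.345 for the additive coefficient and 0.801 for the interaction, and the outer-arm contrast was 0.41 SD against 0.82 SD. In a mixed model fitted to one of these data sets, the additive coefficients (0.157 and 0.282) equalled the arm differences in the pre/post mean.

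**4. Dependence on ρ, with the raw effect held fixed:**

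| ρ | λ interaction | Power, interaction | λ additive | Power, additive |
|---|---|---|---|---|
| 0 | 5.05 | 0.49 | 5.05 | 0.49 |
| 0.3 | 7.21 | 0.65 | 3.88 | 0.39 |
| 0.5 | 10.10 | 0.81 | 3.37 | 0.35 |
| 0.7 | 16.83 | 0.96 | 2.97 | 0.31 |

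**5. Baseline imbalance.** With 30 per arm, one standard error of a baseline difference is √(2/30) = 0.26 SD. Half of it, 0.13 SD, passes into the additive coefficient.

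**6. Baseline adjustment.** The variance of the post-value comparison adjusted for baseline is (1−ρ²)σ², against 2(1−ρ)σ² for change. The ratio is (1+ρ)/2, or 0.75 at ρ = 0.5. Then λ = 10.10/0.75 = 13.47, which with 2 and 86 degrees of freedom gives power of about 0.91. Adjustment therefore improves on the interaction as well.

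**The case against.** The strongest reply is that the sentence only classifies the two factors as fixed rather than random. It does not call the model additive, does not exclude an interaction and does not name the tested coefficient. The differential-improvement hypotheses and the interaction-based power calculation suggest that an interaction was intended, and exact model terms may sit in an analysis plan that is not shown. This stands in part: the Protocol is ambiguous and does not declare a wrong test. But the sentence does specify a model, and fitted exactly as it reads, that model does not answer the Protocol's own question.

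A reader might infer stronger points that the Protocol does not support:

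- *Three incompatible definitions of the test.* Change score and interaction coincide with two complete time points, and the table in Section 5.3.2 names a score without defining an analysis. Only two readings differ.
- *A change-score clash across all mechanism endpoints.* It concerns SART only. Corrugator reactivity, EEG power and sleep latency are per-visit values, and the decrease that defines emotion regulation is a contrast within picture trials, not across the study.
- *A fixed loss of most of the power.* The loss depends on a correlation that is not given, and it is nil at ρ = 0. Section 11.4.4 is also a general calculation, not tied to these endpoints.

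Sections 7.1.4.3 and 11.3.1 do plan a check of baseline differences, with covariates added if needed. That may soften the imbalance problem but does not undo the halving.

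**Conclusion.** The point holds as an under-specified secondary model of moderate severity. Under the literal additive reading the estimate is half the post-treatment effect, whatever the correlation. At N = 90 and d = .335, power is about 0.35 against 0.81 if ρ = 0.5, with the range over ρ as tabulated. These power figures assume 30 completers per arm, equal variances and no class effect. Under the charitable interaction reading nothing is biased, but precision available from the baseline values already collected goes unused. The SART wording clash stands under either reading. No primary conclusion depends on this sentence, and the endpoints are secondary in a pilot, so a higher grade is not warranted. The effect estimates that the pilot is meant to supply do depend on it.

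**What to change.** In Section 11.3.3.1, state that each secondary measure is compared between arms at post-intervention, adjusted for its own baseline. The preferred form is a mixed model with treatment-by-time and a common baseline mean, because it retains participants with missing post values, and Section 11.4.5.1 plans for 15% attrition. Post-value ANCOVA is close to this with complete data. At minimum, name treatment-by-time as the tested term. List the contrasts at post: FA v MBCT, OM v MBCT and FA v OM. Define SART as an error score per visit in both 5.3.2 and 11.3.3.1, and drop the change wording. The cost is about one paragraph of protocol text, with no new data and no added participants.

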#### **Description of outcome variables:**

Attention: Changes in total SART errors (omission/commission)

Emotional Reactivity: Corrugator response ( $\log_{10} \text{ mV}^2$  for the 45–200-Hz EMG band) during first 4s of picture presentation (i.e. before meditation instruction) will be used to assess emotional reactivity to unpleasant relative to neutral pictures. This comparison reflects the traitlike effects of meditation training in the absence of deliberate affect regulation efforts.

Emotion Regulation: The 4-8s post picture onset follows FA or OM meditation instruction and therefore represents the acute affect regulation effects of *active* meditation. Emotion regulation magnitude is defined as the decrease in corrugator EMG power during 4s of meditation vs initial 4s (unregulated) response. All subjects receive both FA and OM instructions, but only the practice that corresponds to the treatment module will be used in analysis (i.e. FA-based regulation for the FA group etc). The average of the combined FA and OM-based regulation will be used for MBCT group.

Wakefulness/Sleepiness: Computer-assisted spectral analysis based EEG measurements of sleepiness will be measured by the mean log transformed power spectral density ( $\text{mV}^2$ ) of 5-9 Hz band at F3/A2, F4/A1 sites for 4 minutes. Neurobehavioral measurement of sleepiness (minutes until sleep onset) will be based on real-time visual analysis of PSG data, including EEG, eye movements, EMG (chin) tone.

#### **11.3.3.2 To determine which neurobehavioral process drives the clinical benefits of mindfulness:**

I chose multiple regression because it can evaluate associations between clinical outcome and multiple correlated continuous and categorical variables (it also fits my training goal of increasing multivariate statistical knowledge). Multiple regression analyses will be conducted across all groups to maximize power and allow for between-treatment comparisons. Criterion variables will include clinical outcome measures of affective disturbance and wellbeing (IDS, DASS, PANAS, WBS) (baseline- 3 month follow-up change scores). Aggregate scores for 1) attention, 2) emotional reactivity/regulation and 3) wakefulness will be entered as separate predictors. Variables that are not equivalent at baseline but may impact outcomes (e.g. sex, education etc) will also be entered as predictor variables. Hypothesized interactions between wakefulness, attention and emotion regulation will be also evaluated using multiple regression.

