**c) Meditation improves PFC-related attention capabilities:** The PFC is involved in different forms of attention including orienting, executive function and alerting (Fan et al., 2002; Fan et al., 2003). Insufficient PFC activation is associated with deficits in attention, such as "difficulty concentrating and making decisions", which are hallmark symptoms of depression. Meditation training is associated with better performance on a wide range of prefrontally-mediated attention tasks (Brefczynski-Lewis et al., 2007; Bushnell, 2009; Chambers et al., 2008; Chan & Woollacott, 2007; [name] et al., 2007; Lutz et al., 2009; Pagnoni & Cekic, 2007; Slagter et al., 2007; Srinivasan & Bajjal, 2007; Tang et al., 2007; Valentine & Sweet, 1999; Wenk-Sormaz, 2005).

**d) Meditation is associated with increased wakefulness:** High levels of blood flow and cerebral metabolic rate in the PFC correspond to alert wakefulness (Buchsbaum et al., 1989; Maquet et al., 1990; Sawaya & Ingvar, 1989), while a hypoactive PFC is associated with fatigue, tiredness and increased sleep propensity (Braun et al., 1997; Buchsbaum et al., 1989; Maquet et al., 1996). Six cross-sectional studies have found EEG-based evidence for increased wakefulness and decreased sleep propensity in meditators (Banquet & Sailhan, 1974; Cahn et al., in press; Cahn & Polich, 2009; Elson et al., 1977; Kaul et al., 2010; Mason et al., 1997) but longitudinal evidence with MBSR interventions is largely based on subjective reports (Carlson & Garland, 2005; Cohen et al., 2004; Singh et al., 1998; Surawy et al., 2005; Tang et al., 2007). In the first objective EEG-based longitudinal RCT of meditation and sleep propensity, I found increased wakefulness and decreased sleep propensity following MBCT that was correlated with improved

depression and meditation practice amount ([name], Haynes et al., 2010) (see Preliminary Studies section).

Together, these studies support the idea that strengthening PFC functioning plays a key role in meditation's beneficial effects. It is unknown which PFC process (attention, emotion regulation, wakefulness) are the most important. This study aims to investigate which of these *processes* (independent of practice type) drives clinical benefit in affective disturbances.

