### **4.3 Exploratory Objectives**

To assess factors other than type of mental training that may impact outcome, including therapist-level (competence) and participant level factors (compliance).

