## 8.5 Participant Compliance with Intervention(s)

### Class Attendance

### Homework Compliance:

Meditation practice logs: Participants keep track of their daily meditation practice during the 8 weeks of active treatment and follow up periods. Diaries include information about meditation practice including: a) the type of meditation (body scan, breath awareness, etc.), b) the number of minutes practiced, c) whether they fell asleep during practice d) use of CD/tape; and informal practice (walking, mindful activities). Logs for the preceding week are collected at each class meeting.

Mindfulness Skill Acquisition: The following inventories will be used to assess the degree to which the participants have acquired various mindfulness skills:

- Five Factors of Mindfulness Questionnaire (FFMQ) (Baer et al., 2006)
- The Mindful Attention Awareness Scale (MAAS) (Brown and Ryan 2004)
- Mindfulness Skill Acquisition([name] & Shahrar, 2003)

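### The Aim 5 regression picks covariates by baseline non-equivalence, which gives meditation practice amount no stated route in, so a process that only tracks practice could be reported as a driver of benefit

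*Protocol*

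**What the plan says.** Protocol section 11.3.3.2 specifies the Aim 5 model. The outcomes are change scores from baseline to the 3-month follow-up. On the predictors it says: "Aggregate scores for 1) attention, 2) emotional reactivity/regulation and 3) wakefulness will be entered as separate predictors". The arms are pooled: "Multiple regression analyses will be conducted across all groups to maximize power and allow for between-treatment comparisons". The covariate rule is: "Variables that are not equivalent at baseline but may impact outcomes (e.g. sex, education etc) will also be entered as predictor variables". Interactions among the processes are also planned. Practice amount and attendance are not named.

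Other sections treat practice differently:

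- Section 8.5: "Participants keep track of their daily meditation practice during the 8 weeks of active treatment and follow up periods". Class attendance is listed there too.
- Section 11.3.2 (primary model): "Level 2 variables will include treatment type, meditation practice amount and demographic variables (age, sex, education".
- Section 11.3.3.1 (Aim 4 model) adds variables identified in the preliminary analysis. Section 11.3.1 includes compliance in that analysis.
- Section 4.3 sets an exploratory objective: "To assess factors other than type of mental training that may impact outcome, including therapist-level (competence) and participant level factors (compliance".
- Section 3.1(d), on the lab's earlier trial: "I found increased wakefulness and decreased sleep propensity following MBCT that was correlated with improved" "depression and meditation practice amount".

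**The concern.** Aim 5 asks which process drives benefit, independent of treatment allocation. It does so by relating change in mood to process scores across individuals. In such a regression the variables to control are those that influence both the process and the outcome. Whether a variable happened to differ at baseline says little about that.

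Practice amount is an obvious candidate. Participants who practise more may train a process more, and may also improve in mood for other reasons such as routine, motivation or expectation. In that case a process coefficient partly measures practice dose, and the process most responsive to practice is favoured whether or not it acts on mood. Section 2.2 intends the findings as pilot data for a later trial of mechanisms, so a mislabelled driver would carry forward.

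**Working it through.** **Which rule can admit practice amount?**

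| Analysis | Covariate rule | Can practice enter? |
|---|---|---|
| Primary (11.3.2) | named list | yes, by name |
| Aim 4 (11.3.3.1) | anything identified in preliminary analysis | yes, since 11.3.1 covers compliance |
| Aim 5 (11.3.3.2) | non-equivalent at baseline | no stated route, since logs start with treatment |

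**Sample size.** The protocol gives no figure for Aim 5, so I use the 90 completers of section 11.4.4. That figure reproduces: f = 0.335/2 = 0.1675. With an assumed repeat-measure correlation of 0.5, the noncentrality is 0.1675² × 90 × 2/(1 − 0.5) = 10.1. On 2 and 87 degrees of freedom the power is 0.805.

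**Model for the check.** All strengths are assumptions; the protocol gives none. Variables are standardised, and higher Y means more improvement.

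- Practice P ~ N(0,1).
- Process j: M_j = aP + noise, j = 1 to 3.
- Mood change: Y = cP + noise. No process affects mood, and c is the path from practice to mood outside the three processes.

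**Expected false coefficient when P is omitted.** With equal a, two processes correlate a², so each coefficient is ca/(1 + 2a²).

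- a = 0.3, c = 0.3: 0.09/1.18 = 0.08
- a = 0.5, c = 0.5: 0.25/1.5 = 0.17
- c = 0: 0 for any a

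**Chance that at least one process is significant at .05.** N=90, 10,000 simulated trials per cell, practice omitted. The nominal rate for three tests is 1 − 0.95³ = 14%.

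| Outside path c | a = 0.3 | a = 0.4 | a = 0.5 |
|---|---|---|---|
| 0 | 14% | 14% | 14% |
| 0.1 | 16% | 16% | 17% |
| 0.2 | 21% | 23% | 26% |
| 0.3 | 30% | 36% | 40% |
| 0.4 | 40% | 52% | 57% |
| 0.5 | 54% | 68% | 75% |

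Repeat runs with other seeds put the last cell at 76% to 78%, so about 76% is a fair summary. With P in the model every cell returns to about 14%.

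**Unequal case.** Suppose practice moves wakefulness more (0.5) than the other two (0.2). Wakefulness is then falsely flagged in about 26% to 61% of trials for c = 0.3 to 0.5, 13% for c = 0.2 and 7% for c = 0.1. With P in the model the rate is 5%.

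**Cost of adjusting.** Take a true process effect of 0.3, practice correlated 0.5 with that process only, and c = 0. Both models estimate 0.30. Adjustment multiplies the standard error by √(1/(1 − 0.5²)) = 1.15, and power falls from about 81% to 70%. If practice correlates 0.5 with all three processes, power falls from about 78% to 70%.

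**The case against.** A reader might infer three stronger things that the protocol does not support.

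1. *That the pilot tied practice to depression.* Section 3.1(d) correlates the wakefulness change with practice amount and with improved depression. It reports no correlation between practice and depression. The pattern fits practice acting on mood through wakefulness equally well.
2. *That practice can never enter the Aim 5 model.* The rule is not worded as exclusive, and section 11.3.1 examines compliance for patterns that may affect later analyses. What is missing is a stated route such as section 11.3.3.1 gives.
3. *That misattribution will occur.* It needs a path from practice to mood outside attention, emotion regulation and wakefulness. Sections 2.2 and 3.1 hypothesise that meditation works through these prefrontal functions. If it works wholly through them, omitting practice causes no bias. Section 4.3 says compliance may affect outcome, not by what route.

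It can also be said that Aim 5 is secondary, that section 11.4.1 aims at estimation more than significance, that covariate lists are often left to an analysis plan, and that adjusting costs power. At an assumed process reliability of 0.7, a simulation of the same kind (true effect 0.3, correlation 0.5, c = 0) gives a fall from 62% to 50%.

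Most of this stands, and it rules out resting every claim on the adjusted coefficient alone. It does not remove the point. Section 11.3.3.2 does state a selection rule, on a criterion unsuited to this regression and narrower than those of its neighbouring analyses. The design cannot tell in advance whether an outside path exists.

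**Conclusion.** The point holds as an inconsistency with a conditional consequence. Section 11.3.3.2 selects Aim 5 covariates by baseline non-equivalence and gives practice amount no stated route in, although the primary and Aim 4 models do, the pilot correlated wakefulness change with practice, and compliance is listed as a possible influence on outcome.

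The size depends wholly on assumed strengths. The error is serious if practice has a moderate outside path to mood (0.3 or more), small at 0.1, and absent at zero. The protocol does not show which case applies. Comparing the two fits would show how far each process result depends on practice. This is worth changing before analysis, but it does not undermine the trial's primary comparison.

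**What to change.** In section 11.3.3.2, add that every Aim 5 regression will be fitted with and without total practice minutes from the 8-week treatment logs and number of classes attended, whatever the baseline comparison shows. Report both sets of process coefficients. Describe a process as driving benefit only with a statement of whether its coefficient persists after adjustment. Use the treatment-phase logs because section 5.2 schedules the laboratory process measures before and after treatment, so follow-up practice comes after them.

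The cost is a sentence or two in the plan, up to two degrees of freedom and no new data. The adjusted coefficient loses some power (about 80% to 70% in the case above). Self-reported logs also make the adjustment partial: with an assumed log reliability of 0.7, c = 0.4 and practice moving wakefulness most, adjustment cuts the false wakefulness rate from 42% to 9%, not to 5%.
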